## Abstract

**Background:**

Unhealthy alcohol use (UAU) is a leading cause of premature mortality among adults in the USA. Emergency departments (EDs) are key intervention settings for UAU but often have limited time and resources. One low-burden, scalable approach to address UAU is text-messaging interventions. Despite strong research support and promise for scalability, there is little research on how to implement such interventions in healthcare settings. The process of providers making them available to patients in an efficient way within already busy and overburdened ED workflows and patients adopting them remains a new area of research. The purpose of this three-phase study is to develop and test an implementation strategy for UAU text-messaging interventions in EDs.

**Method:**

Our first aim is to examine barriers and facilitators to staff offering and patients accepting a text-messaging intervention in the ED using an explanatory, sequential mixed methods approach. We will examine alcohol screening data in the electronic health records of 17 EDs within a large integrated health system in the Northeast and conduct surveys among chairpersons in each. This data will be used to purposively sample 4 EDs for semi-structured interviews among 20 clinical staff, 20 patients, and 4 chairpersons. Our second aim is to conduct a stakeholder-engaged intervention mapping process to develop a multi-component implementation strategy for EDs. Our third aim is to conduct a mixed method 2-arm cluster randomized pilot study in 4 EDs that serve ~11,000 UAU patients per year to assess the feasibility, acceptability, and preliminary effectiveness of the implementation strategy. The Integrated Promoting Action on Research Implementation in Health Services framework will guide study activities.

**Discussion:**

Low-burden technology, like text messaging, along with targeted implementation support and strategies driven by identified barriers and facilitators could sustain large-scale ED-based alcohol screening programs and provide much needed support to patients who screen positive while reducing burden on EDs. The proposed study would be the first to develop and test this targeted implementation strategy and will prepare for a larger, fully powered hybrid effectiveness-implementation trial. Findings may also be broadly applicable to implementation of patient-facing mobile health technologies.

**Trial registration:**

This study was registered at ClinicalTrials.gov (NCT05350878) on 4/28/2022.

Contributions to the literature
Emergency departments are important venues for addressing unhealthy alcohol use; however, given the limited time and resources, low-burden interventions are needed in this setting.Text-messaging interventions are low burden and potentially scalable in emergency departments to address unhealthy alcohol use, but limited research has examined their implementation.This study will examine barriers and facilitators to implementation of text-messaging interventions for unhealthy alcohol use in emergency departments and develop and test a multi-component implementation strategy.Study findings may be broadly applicable to the implementation of patient-facing mobile health interventions for substance use in ED settings—an understudied research area.

## Background

Unhealthy alcohol use (UAU) is estimated to cost the USA over $200 billion per year [1] and is one of the leading causes of premature mortality among adults [2, 3]. UAU is defined as a continuum of behaviors from risky or harmful use (exceeding recommended daily, weekly, or per occasion amounts) to alcohol use disorder [2]. National data suggests that, of the over 140 million current alcohol users, 47% exceeded recommended per occasion drinking amounts [4]. An estimated 14.5 million adults meet criteria for alcohol use disorder [4]. The prevalence of UAU was increasing among adults prior to the COVID-19 pandemic and the pandemic has further exacerbated UAU and related negative consequences [2, 5–7].

Emergency department (ED) visits involving alcohol consumption have increased in recent years [8] and UAU is more common among ED patients than in the general population [9]. It has been posited that substance use is the most important modifiable health behavior in the ED, [10, 11] as such the ED has been highlighted as a key intervention setting for UAU [12, 13]. Health systems are being tasked now more than ever with addressing substance use among their patients but often have limited time and resources [10]. ED clinicians work in high-volume, high acuity settings with significant time constraints and little training in providing intervention for substance use problems [10]. The ED is a promising point of intervention, yet scalable supports that reach as many patients with UAU as possible are needed.

Leveraging simple and efficient technology to support behavioral health intervention implementation in EDs has been urged [10, 14, 15]. The vast majority of ED patients (90%) express a strong preference for receiving health interventions via technology [15]. Access to mobile technology among ED patients who use substances is high: 97% report cell phone usage and many report a preference for technology-based means of receiving information about substance use [10]. Text messages are one of the most basic modes of mobile health interventions and use brief, supportive electronic messages transmitted via a mobile phone network to promote behavior change and may be the lowest burden, most preferred mobile health format [16–18]. Over the past decade, text-capable mobile phones have become ubiquitous across socioeconomic classes [19, 20]. It has been posited that text-message interventions have the potential to reduce health disparities at low cost because they appeal to the most underserved communities, including those that do not connect with traditional healthcare services [21]. Texts cost a fraction of a penny to send and unlimited texting plans are common [18, 22]. Interventions using text messages are low burden in that receiving intervention messages requires no user effort. They do not require logging in, tunneling through web pages, time-consuming data entry fields, or downloading an app [23]. Other advantages include being able to provide support over time in an individual’s natural environment and adapting content based on changing circumstances and feedback from the recipient [23]. From the health system perspective, text-messaging programs are relatively inexpensive to develop and maintain, do not require formal design, are agnostic to operating system, and expensive updates are not needed [18]. Text-based interventions may be the most feasible option for ED patient populations given the challenges of providing face-to-face intervention in EDs and they have the potential to reach traditionally underserved populations [15].

Reviews of text-messaging interventions for health behaviors broadly have found that the majority were effective and that there is strong evidence to support the value of integrating them into public health practice [18, 23, 24]. Text interventions are an acceptable and feasible strategy to enhance the delivery of care for persons with substance use problems [17, 25–27]. A recent meta-analysis found that text-messaging alcohol interventions reduce alcohol consumption compared with no or basic health information [28]. For example, people with harmful drinking patterns significantly reduced drinking frequency and quantity after receiving daily texts [29]. Patients with alcohol use disorder perceive that text interventions may help them remain abstinent [30]. The benefits of harnessing text interventions for UAU in the ED could be considerable because they are low burden for patients and acceptable and effective [31]. For example, discharged trauma center patients who received a text intervention reduced hazardous drinking as compared to usual care controls [32] and the majority of trauma patients would enroll if offered a text intervention [33]. Among patients recruited from EDs, text interventions for UAU are effective in supporting them in meeting drinking goals and making drinking reductions, including reductions in binge drinking and number of drinks consumed per day [34, 35]. Furthermore, 44% of ED patients accepted a text intervention and those who accepted had higher rates of treatment attendance after discharge from the ED as compared to those who did not accept [9]. These studies show broad efficacy for text interventions in EDs with potential to reach diverse populations; however, no studies have developed and tested a strategy for systematically offering them to patients in EDs in a scalable manner.

Systematic reviews have noted that very few studies examine implementation and dissemination of mobile health technology [10, 36, 37]. Recent failures of pragmatic mobile health trials due to lack of patient and staff uptake are a warning that careful implementation approaches are needed [38, 39]. A complex web of inter-related technical, social, patient, and organizational considerations may be at play [40–42]; yet insufficient guidance is available to inform larger scale implementation of mobile health [10, 12, 15, 17, 19, 23, 43–45]. Two recent reviews of substance use technology interventions noted that only one study [46] focused explicitly on implementation outcomes; most focused only on patient clinical outcomes [37, 47]. Few of these studies mention implementation strategies, making it difficult to know how to successfully implement technology into practice [37]. Other reviews urge the field to move toward developing text intervention implementation strategies [17, 48], with one stating that “the field awaits true dissemination and implementation studies in which text interventions are put into place in real world settings.” [18]. Research should prioritize examining techniques for increasing uptake of alcohol text interventions among patients as well as examining whether ED staff are likely to systematically offer such interventions [9].

Implementation of text interventions for UAU will require EDs to address patient, setting, administrative, and staff barriers. This study will use the Integrated Promoting Action on Research Implementation in Health Services (i-PARIHS) framework to guide intervention and research activities [49, 50]. i-PARIHS posits that optimal implementation occurs when practice facilitation promotes the acceptance and use of a new practice innovation based on both the recipient’s needs and on the unique nature of the inner and outer context [50, 51]. i-PARIHS positions facilitation as the active ingredient to help navigate individuals and teams through complex change processes by addressing (a) the innovation’s degree of fit within the existing practice; (b) the motivations, beliefs, characteristics, and resources of the intervention recipients; and (c) the inner and outer context (e.g., leadership support, culture, the learning environment, organizational priorities, capacity for change, mandates). Facilitation has been defined as interactive problem solving that is active, dynamic, and task-oriented and has been used in a number of disciplines [50, 52, 53]. Notably, facilitation has been utilized for several decades and has now become routine for implementing changes [54–56]. ED-based studies have started to use facilitation along with comprehensive implementation strategies because typical strategies such as educational sessions or grand rounds presentations are not enough to implement new practices successfully [57]. However, i-PARIHS does not dictate specific implementation strategies given that each context, recipient, and intervention may call for a different set of strategies. Selecting implementation strategies is a complex task and strategies are too often selected in an unsystematic way, fail to address key contextual determinants, and are not well matched to the contexts in which they are deployed [58]. Rigorous methods are needed to select strategies that take into account relevant theory and stakeholder participation and that are specified clearly enough to be replicated [59, 60]. This study will use a systematic intervention mapping process to develop the facilitated implementation strategy [59, 61–64]. The aims of this study are to:

Aim 1: examine potential barriers and facilitators to staff offering and patients accepting a text-messaging intervention in the ED using an explanatory, sequential mixed methods approach

Aim 2: use a stakeholder-engaged intervention mapping process to develop a multi-component implementation strategy for EDs

Aim 3: conduct a mixed method 2-arm cluster randomized pilot study in 4 EDs that serve ~11,000 UAU patients per year to assess the feasibility, acceptability, and preliminary effectiveness of the implementation strategy

## Methods

### Aim 1: Identify barriers and facilitators to implementing a text-messaging intervention for UAU in EDs

#### Design

The study will be conducted within a large integrated health system in the Northeastern United States that has 17 EDs serving adult patients. For aim 1, we will use an explanatory, sequential mixed methods approach that places more emphasis on the qualitative data (quant → QUAL) [65] given that little is known about barriers/facilitators to text-messaging intervention implementation in EDs. First, we will examine alcohol screening data in the electronic health records (EHRs) of the 17 EDs and conduct surveys among chairpersons in each. This data will then be used to purposively sample 4 EDs for semi-structured interviews among clinical staff (e.g., nurses, physicians), patients, and chairpersons (2 with low perceived implementation barriers; 2 with high perceived barriers).

#### Quantitative data sources, sample, and analysis

All EDs in this study use the structured, validated 3-item AUDIT-C screening tool [66] to detect UAU. It is built into their EHRs which capture screening results and reasons for screening deferral if applicable (e.g., acuity of illness, including mental status and intoxication) or patient refusal. Data on alcohol screening from the past 12 months will be extracted and compiled from the EHRs of the 17 EDs to include: % patients screened (numerator: # AUDIT-C screens completed; denominator: total patient census) and % screenings deferred (numerator: # patients with AUDIT-C screening deferral indicated; denominator: total patient census). EHR data on alcohol screening is being examined because it provides an important clue to each ED’s buy-in and ability to identify and address UAU. For example, EDs with low screening completion rates may indicate staff hesitancy, lack of time to screen patients, or an EHR where the AUDIT-C has no reminder prompt for completion. Such factors may limit ED’s ability to properly identify appropriate patients and offer them a text intervention. ED chairpersons (or their designee) of each of the 17 EDs will complete a 12-item online survey measuring their views on the feasibility, acceptability, and appropriateness of implementing a text-messaging intervention in EDs that is adapted from a validated measure [67]. We will calculate an average score for each chairperson.

#### Qualitative data sources, sample, and analysis

We will identify 4 ED sites (2 with low perceived implementation barriers and 2 with high perceived barriers) for semi-structured interviews using stratified purposeful sampling [68, 69]. We will create low and high categories based on ED alcohol screening completion rates (low = ≤ median; high = > median) and survey score (low = score ≤ median; high = above the median).

##### ED chairperson and staff

In each of the 4 selected EDs, chairpersons who completed the quantitative survey will be interviewed. Modeled on other implementation studies [70], we will then ask each chairperson to identify 5 clinical staff for interviews (e.g., nurses, physicians, support staff). Interviews (~30 min) will be conducted over the phone or in-person depending on staff preference. If conducted over the phone, we will follow best practices for phone-based qualitative interviews in health services research [71, 72]. Interview guides for staff, informed by the i-PARIHS framework [57, 73], will cover views on alcohol screening in the ED, text-messaging interventions and how to best offer them to patients, and barriers/facilitators to intervention implementation and general practice change.

##### ED patients

To recruit patients for interviews, following procedures from similar ED studies [10], patients will be approached in the ED if they screened positive on the AUDIT-C (≥3) as identified in the EHR. We will recruit 5 patients from each of the 4 EDs. Interviews (~30 min) will be conducted in a private area in the ED and patients will be offered a $15 gift card. If saturation is not reached with the initial samples, additional interviews will be conducted. Interview guides for patients will be adapted from a study that assessed patients’ preferences and attitudes toward technology interventions initiated in the ED [15] and a semi-structured interview guide used among trauma patients on this topic [33] (e.g., mobile device ownership and use, interest in receiving supportive messages via mobile device on UAU reduction, best ways to offer patients the intervention in the ED, concerns about using mobile devices). Expert consultants in implementation science and ED-based text messaging will provide feedback on interview guides.

##### Qualitative analysis

Interviews will be recorded and transcribed then analyzed using directed content analysis [74]. We will use a deductive approach such that a codebook with codes and operational definitions will be created prior to analysis using key elements from i-PARIHS [75]. A two-person coding team, led by the first author, will be used. We will use Atlas.ti to manage, organize, and examine patterns in the data and will follow recommended steps for content analysis [75, 76]: (1) transcripts will be read several times by coding team, (2) meaning units within the transcripts will be identified (i.e., smallest amount of text that contains needed insights) [75], (3) meaning units will be coded; data that cannot be coded using initial codes will be identified and analyzed after initial coding to determine if they represent a new category or sub-category of an existing code [74], (4) codes will be sorted into categories, and (5) themes will be formed by grouping two or more categories together. Coding disagreements will be resolved through discussion. We will use a continuous process of coding, categorizing, and reviewing the raw data to reflect on the analysis at various points and make revisions (e.g., recoding data). Weekly coding meetings will be held to review coding decisions, discuss discrepancies, and check progress. We will use several methods to increase trustworthiness [77]: sample to the point of saturation, conduct negative case analysis, use member checking, keep an audit trail on study decisions, maintain a detailed codebook, and track inter-coder reliability.

### Aim 2: Develop a stakeholder-driven multi-component strategy for implementation of a text-messaging intervention for UAU in the ED

We will use a systematic 4-step intervention mapping method [59, 61–63] to develop our implementation strategy. We will leverage aim 1 results and three stakeholder meetings. Stakeholder meetings will consist of ED chairpersons, administrators, staff, and patients from within the integrated health system where the study is being conducted as well as ED stakeholders external to the health system. The intervention mapping approach will create a transparent, deliberate, stakeholder-engaged process while aligning with strategies and terminology in the implementation science literature.

#### Intervention mapping: step 1

The first step is a needs assessment. The study team will compile results from aim 1 quantitative and qualitative data to assess implementation needs.

#### Intervention mapping: step 2

Aim 1 results will be presented to a stakeholder group consisting of ED staff, chairpersons, administrators, patients, and expert consultants to identify concrete objectives and expected outcomes of the implementation strategy. For example, the group will identify what would need to be changed at the setting, patient, staff, and administrative levels for successful implementation of the text intervention. The study team will create a matrix of needs, goals, and objectives for successful implementation resulting from this meeting.

#### Intervention mapping: step 3

This step involves identifying theory-based, practical discrete implementation strategies to meet the needs, goals, and objectives from step 2. The study team will select implementation strategies with the following principles in mind: (1) appropriateness for the ED setting, (2) replicability and generalizability, (3) feasibility and sustainability for future dissemination, and (4) alignment with the i-PARIHS components to address ED needs, constraints, resources, and context. Implementation strategies will be selected from the i-PARIHS facilitator’s toolkit [49] and other expert-consolidated implementation strategy lists [78] and the following will be identified for each implementation strategy chosen: active ingredient, causal mechanisms by which they will exert the desired changes, mode of delivery (e.g., face to face), and the intended target (e.g., administrators, front-line staff, patients) [79]. See Fig. 1 for sample implementation strategies mapped onto the i-PARIHS framework. Guided by the i-PARIHS framework, we will use practice facilitation, and an internal-external facilitator team will support sites’ use of the identified implementation strategies. Internal-external facilitation is used commonly [80, 81] and leverages internal provider motivation with outside expertise and program support [50, 82]. The second stakeholder meeting will be used to receive feedback on and refine the selected implementation strategies.

**Fig. 1 Fig1:**
[figure not shown]
The i-PARIHS model and example implementation strategies and outcomes

#### Intervention mapping: step 4

The multi-component implementation strategy will be designed, and its execution planned in the final step. The strategies identified in step 3 will be operationalized to clearly delineate what they entail, as well as how they will be delivered. Materials (e.g., manuals, training materials) to support the implementation strategy will also be created. The third stakeholder meeting will be held to get feedback on the execution plan and materials.

### Aim 3: Examine the feasibility, acceptability, and preliminary effectiveness of the implementation strategy

#### Design

In line with recommendations pertaining to the scope and target outcomes of pilot studies for implementation trials [83–85], the main goal of this pilot trial is to assess the (1) feasibility (i.e., perceptions among ED clinical staff members that the implementation strategy can be successfully used), (2) acceptability (i.e., perceptions among ED clinical staff members that the implementation strategy is agreeable, palatable, or satisfactory), and (3) and preliminary effectiveness of the implementation strategy. We will operationalize our effectiveness outcome as “reach” (i.e., proportion of eligible patients that enroll in the text intervention), which is a key outcome recommended in the implementation science literature [83, 85–87]. The design is a mixed method, two-armed, study in 4 EDs (2 assigned to the new implementation strategy vs. 2 implementation as usual control). Qualitative and quantitative measures will be collected and analyzed simultaneously and merged—qualitative data will provide context to and explanation of the quantitative results in a complimentary way, representing a QUAL + QUAN structure that gives equal emphasis to both types of data [65].

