#### Data sources and measures

##### Effectiveness/reach

Effectiveness will be examined by calculating how many patients were eligible (positive AUDIT-C) based on EHR data and the proportion who enrolled in the intervention as collected by the text platform. Demographics will also be collected from the EHR and text platform to examine differences in characteristics between who was eligible based on AUDIT-C score and who enrolled. In the text platform, each study site will have a unique enrollment text code number, allowing for tracking of patients that enrolled by site and when they enrolled, demographics, and responses to the intervention tailoring questions (e.g., drinking patterns, self-efficacy, motivation). We anticipate there will be ~5000 UAU eligible patients identified during the study trial period based on (1) sites’ current census, (2) current screen positive rates, and (3) screening completion rates based on our previous evaluations in this integrated health system.

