#### Analysis

The same procedures described in aim 1 will be used to analyze qualitative data for aim 3. For the reach/effectiveness quantitative data, we will calculate a proportion for each study condition (e.g., numerator: # of patients in control or intervention sites who enrolled in the intervention; denominator: # of patients with positive AUDIT-C) and use *z*-tests for independent proportions [93] to examine whether control and intervention sites differ significantly. We will also use *z*-tests to examine differences in demographics between those eligible and enrolled to determine whether there are gender or racial disparities. For these proportional analyses [94], to achieve 80% power, a sample size of at least 300 in each condition is needed (total of 600) to detect a 10% difference in proportions with significance level of *p* = .05. For the feasibility/acceptability staff and patient survey data, we will calculate descriptive statistics for each. We will triangulate this quantitative data with the qualitative data by merging the results. No identifying information will be maintained by the study team for any staff or patients; all participants will be identified with a participant ID.

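### Reach is divided by AUDIT-C positives counted after randomisation, a number the strategy could itself change; a census-based supporting measure and a screening table would show whether it did

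*Protocol article*

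**What the plan says.** **Outcome.** In the protocol article, Aim 3, Design makes reach the effectiveness outcome: the "proportion of eligible patients that enroll in the text intervention". Aim 3, Effectiveness/reach describes the calculation: "calculating how many patients were eligible (positive AUDIT-C) based on EHR data and the proportion who enrolled in the intervention as collected by the text" (the closing words refer to the messaging system). Aim 3, Analysis repeats the choice ("denominator: # of patients with positive AUDIT-C") and compares the two conditions with a z-test for independent proportions.

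**Screening.** Aim 1, Quantitative data sources, sample, and analysis measures completion as "numerator: # AUDIT-C screens completed; denominator: total patient census", and deferral over the same census. It notes that "EDs with low screening completion rates may indicate staff hesitancy, lack of time to screen patients", or an AUDIT-C without a reminder in the EHR, and that such factors may limit an ED's "ability to properly identify appropriate patients and offer them a text intervention".

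**Strategy.** Aim 2, Intervention mapping step 3 will specify for each chosen component, among other things, "the intended target (e.g., administrators, front-line staff, patients". Aim 3, Implementation strategy condition gives the strategy EDs seven months of facilitation: two to prepare policies and workflows for making the offer, and five of active support. Aim 3, Control condition gives the other EDs an information session and flyers, and no facilitation.

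**Balance.** Aim 3, Study site randomization balances annual census, location and AUDIT-C positive rate. Screening completion is not on that list.

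**The concern.** A positive AUDIT-C exists only where a screen was completed, and the positives that count are those recorded during the trial. The denominator is therefore a post-randomisation count, not a population fixed at baseline. The protocol itself links completion to staff attitude and time, and only one arm receives an intervention that may work on front-line staff and their workflows.

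If the strategy also changed who gets screened, a difference in reach would mix two things: how often identified patients enrol, and how many patients are identified. A strategy that improved screening could show no gain in reach despite more enrolments. One that led staff to screen fewer or more receptive patients could show a gain without more enrolments.

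This matters because, according to the Discussion, preliminary effectiveness feeds the decision on a larger trial, alongside feasibility and acceptability. The analysis stated in the article includes no comparison that would separate the two explanations.

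**Working it through.** **Inputs from the protocol article.** About 5,000 eligible patients during the trial (Effectiveness/reach); 4 EDs, 2 per arm (Design); at least 300 per condition for 80% power to detect a 10-point difference at p = .05 (Analysis); a 44% acceptance rate from a cited ED study (Background).

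**Assumptions.** An equal split, so 5,000/4 = 1,250 positives per ED and 2,500 per arm. Control reach is not stated, so it is varied. Screening completion rates are not given either; those below are illustrative.

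**1. The plan's own figure.** The pooled two-sided formula is n = [1.96·√(2p̄q̄) + 0.84·√(p₁q₁ + p₂q₂)]² / 0.10². For 20% against 30% it gives 294 per condition (power 0.809 at 300); for 21% against 31% it gives 301. The stated 300 therefore fits a control reach of about 20%, which is why 20% is the central case here. The point does not depend on that figure.

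**2. How the measures relate.** Let C be census, S completed screens, P positives and E enrolments. Then E/C = (S/C) × (P/S) × (E/P). Reach is the last factor only. If the strategy changes S/C or P/S, reach and enrolments per census can move differently.

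**3. One ED, illustrative completion rates.** Start at 60% completion, 1,250 positives and 250 enrolled, so reach is 250/1,250 = 20%. With everyone screened there would be 1,250/0.60 = 2,083 positives, holding the positive rate constant.
- Completion rises to 80%: 2,083 × 0.80 = 1,667 positives. If 20% still enrol, that is 333 enrolments, a third more, and reach stays at 20%.
- Completion falls to 40%: 2,083 × 0.40 = 833 positives. If the same 250 enrol, reach is 250/833 = 30%. This is the extreme case, because it needs every eventual enrollee still to be screened.

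**4. The planned z-test with equal enrolments.** z = (E₁/P₁ − E₂/P₂) / √[p̄(1 − p̄)(1/P₁ + 1/P₂)], control arm 500/2,500 = 20%.
- Strategy arm 500/2,000 = 25%: p̄ = 1,000/4,500 = 0.222, SE = 0.01247, z = 0.05/0.01247 = 4.01, p = 0.00006.
- Strategy arm 500/3,125 = 16%: p̄ = 1,000/5,625 = 0.178, SE = 0.01026, z = −3.90, p = 0.0001.
- Strategy arm 750/3,750 = 20%: z = 0, despite 50% more enrolments.

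**5. Change in the strategy arm's positives that gives p < .05, or a 10-point gap, with equal enrolments.** The 10-point factor is r/(r + 0.10), where r is control reach.

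| Control reach | Fall for p < .05 | Rise for p < .05 | Denominator ratio for +10 points |
|---|---|---|---|
| 10% | 15% | 18% | 0.50 |
| 20% | 10% | 12% | 0.67 |
| 30% | 8% | 9% | 0.75 |
| 44% | 6% | 7% | 0.82 |

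At 5% control reach, a 20% fall gives 6.25% against 5% and does not reach significance (p = 0.069).

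**The case against.** The strongest reply is that the mechanism is inferred. The facilitation is described as support for making the offer, which comes after a positive screen. Screening is already built into the EHR at all sites, and both arms are told that patients who screen positive under the site's own procedure are appropriate. The strategy has yet to be designed. Aim 1 says low completion may indicate hesitancy or lack of time, as an example for comparing 17 EDs; the deferral reasons it lists concern the patient's condition or refusal. No section states who administers the AUDIT-C. All of this stands, and it limits the point to what could happen.

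Second, enrolled over eligible is a legitimate definition of reach. A strategy for offering texts to identified patients can fairly be judged among identified patients. If screening rises and the same share enrols, unchanged reach is the right answer to that question. This also stands, so the definition should stay.

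Third, the 40% completion case is extreme, and the low thresholds for p < .05 come partly from a test that treats about 2,500 patients per arm as independent across four EDs, which is a separate matter. The study is also a pilot, with qualitative data given equal weight. These replies reduce the weight of the figures but not the identity in step 2 of the working.

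A reader might infer that the strategy will distort the denominator, or that reach should count only if a census-based measure agrees. The documents support neither. They give no direction or size for any effect on screening. Enrolments per census answer a different question and can legitimately differ from reach, so they should not be able to veto it.

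**Conclusion.** The point holds as a possibility that the stated analysis would not detect. The denominator is fixed by the article as a count made after randomisation; the article says completion may depend on staff; and facilitation goes to one arm only. Balancing on the baseline positive rate addresses neither completion nor later change.

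At an assumed 2,500 positives per arm and control reach of 10% to 44%, a fall of 15% to 6% or a rise of 18% to 7% in the strategy arm's positives would give p < .05 with identical enrolments. These sizes rest on the equal split, the assumed reach and the patient-level test; they do not forecast what the strategy will do. That staff carry out the screening is inferred from Aim 1. An analysis plan that is not shown may already include the screening data. The point is therefore a cheap improvement in how reach can be interpreted, not an error in its definition or arithmetic.

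**What to change.** Keep enrolled over eligible as the reach outcome. In Aim 3, Analysis, add as supporting information:

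- enrolments per adult ED census over the same window, by ED and by arm;
- screening completion, deferral and AUDIT-C positive rates by ED, before and during the trial, from the EHR, with completion and deferral defined as in Aim 1.

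State how they will be read: if reach and enrolments per census differ in direction, interpret the reach difference in light of the screening data and do not attribute it to better offering alone. Do not make agreement between the two a formal condition.

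The cost is one more denominator from the EHR and a short table. Enrolments per census will be a smaller and less intuitive percentage, and it also moves with screening, which is why it supports reach and does not replace it.
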